### Inclusion criteria

1. Age between 18 and 45 years
2. Sufficient understanding of the German language
3. Subjects understand the procedures and the risks associated with the study
4. Participants must be willing to adhere to the protocol and sign the consent form
5. Participants must be willing to refrain from taking illicit psychoactive substances during the study.
6. Participants must be willing to drink only alcohol-free liquids and no xanthine-containing liquids (such as coffee, black or green tea, red bull, chocolate) after midnight of the evening before the study session. Subjects must agree not to smoke tobacco for 1 h before and 4 hours after MDMA administration.
7. Participants must be willing not to drive a traffic vehicle in the evening of the study day.
8. Women of childbearing potential must have a negative pregnancy test at the beginning of the study and must agree to use an effective form of birth control. Pregnancy tests are repeated before each study session.
9. Body mass index: 18-25 kg/m2

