## Schedule of experimental session

**Table 2** shows the schedule of events for each experimental session. Each of the four test sessions will last 10 h from 8:00 AM to 6:00 PM. Subjects will arrive at 8:00 AM at our CRC. Subjects will take duloxetine (120 mg) or placebo the night before the study session at 8:00 PM and another dose of duloxetine (120 mg) or placebo in the morning of the study day (8:00 AM). An indwelling intravenous catheter will be inserted into a subcutaneous vein of the forearm of the nondominant arm. MDMA (125 mg) or placebo is administered 4 h after duloxetine (12:00 AM). The acute effects of MDMA are expected to last for 4 h [42, 43]. Outcome measures (see below) will repeatedly be assessed during the study session. The sessions end at 6 PM. Subjects will be under continuous medical control until the effects of the drug have completely subsided (within 4-6 h after MDMA administration).

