#### List of complaints (LC) and Adverse effects (AE)

Adverse effects (AE) will be assessed systematically during the session using a modified list of complaints (LC) [54]. The scale consists of 66 items, yielding a global score measuring physical and general discomfort. The LC list is administered 4 h before and 180 min after MDMA/placebo. An additional LC is completed 24 h after MDMA/placebo in the absence of the experimenter. Additional AE during the session will be listed in the case report form (CRF) 5 h after MDMA/placebo administration. Subjects will also be asked to report AE between study sessions at the beginning of the next session.

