# Protection of subjects

Trained study personnel will place venous accesses, administer the study drugs and collect blood samples. Subjects will be supervised by trained study personnel during the entire test sessions, backed-up by study physicians. After the test session subjects are allowed to leave only if the subjective and cardiovascular effects of MDMA have completely ceased (see 14.2.5). In the case of unexpected prolonged or severe adverse reactions subjects will remain at the CRC and are monitored as long as necessary. Subjects will be provided with the phone number of the study physician on call in case of an emergency between/after study sessions.

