## Potential risks

Physical risks:

MDMA: A large series of phase I like studies have been performed using MDMA [13-16, 24, 42, 44-47, 57, 58, 67, 68, 70, 71, 74, 75, 82-91]. This considerable body of evidence indicates that the likelihood for significant toxicity from doses of MDMA such as the one to be used in the present study and in controlled settings is very low. Thus, no lasting biological or psychological injury is expected. See below for specific MDMA toxicity and monitoring. Expected adverse effects of MDMA:MDMA is expected to produce moderate acute adverse effects such as increased jaw muscle tension, dry mouth, dizziness, palpitations, tremor, nausea, headache, insomnia, and transient anxiety in more than 10% of subjects, [15, 42]. MDMA is expected to produce sequelae (1-3 days post MDMA) including difficulty concentrating, irritability, or slightly depressed mood in more than 10% of subjects [15]. No severe or serious adverse effects are expected. Duloxetine: In placebo-controlled double-blind trials in patients duloxetine (60-120 mg/day) produced nausea (20-29%), headache (20%), dry mouth (15-18%), insomnia (11-15%), fatigue (14%), dizziness (9-11%), constipation (11%), decreased appetite (8%), and sweating (6%) [63]. Adverse effects of duloxetine in healthy volunteers similary include nausea, dry mouth, insomnia, dizziness, sweating, and clinically non-significant increases in blood pressure or heart rate [25, 61, 92]. No severe or serious adverse effects are expected.

Venipunction: There is a risk for pain, bruising and thrombophlebitis.

Risk to privacy of subjects: Potential risks of data collection include breach of confidentiality. Financial risks: There is no risk of expense to the subject. Insurance coverage is provided. Travel expenses are expected to be minimal and are included in the compensation of 1000 CHF per subject.

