### Monitoring for specific toxicity

Duration of monitoring: Subjective and cardiovascular effects of MDMA last for a mean of 3.5 h and completely subside within 5-6 h [13, 42, 43, 58, 67]. Accordingly subjects are monitored for 6 h after MDMA administration. In our previous studies, that similarly evaluated interactive effects of MDMA with various pretreatments, subjects were dismissed 4 h after MDMA administration [13, 15, 68, 82]. Another interaction study used an observation time of 6 h after MDMA administration similar to the present study [43]. Only one to two subjects are tested simultaneously on the same test day.

Cardiovascular effects: Blood pressure and heart rate are measured at repeated intervals (Table 2). Closer monitoring will be implemented if blood pressure values exceed 180/120 mm Hg. Subjects will be monitored for signs of hypertensive crisis such as headache, angina pectoris or neurological deficits. Treatment of a hypertensive reaction (Psys>220 mmHg) would include administration of oxygen, lorazepam, nitroglycerin or nifedipin or/and carvedilol. In the case of angina pectoris, oxygen is given and ECG monitoring is initiated and cardiac enzymes will be measured. Subjects will remain at the CRC overnight for further observation if blood pressure is >140/95 mmHg or pulse rate is >100/min at the end of the test session at 6 PM.

Psychological effects: The effects of MDMA are mostly pleasurable. Dysphoric reactions to MDMA and moderate anxiety may occur at the onset of the MDMA effect. Such effects have always resolved within hours [42]. Unexpected severe anxiety would be treated with a benzodiazepine. Up to one third of the subjects is expected to experience slightly depressed mood including emotional irritability, lack of energy, brooding and bad dreams for up to 3 days following MDMA administration [42]. These effects will be specifically monitored using an adverse effects check list. After the test session subjects are allowed to leave only if the subjective effects of MDMA have completely ceased (VAS score “drug effect” back to predose ± 10%).

Hyperthermia: Increases in body temperature of approximately 0.5C are expected [42]. If body temperature rises by more than 1.5C appropriate treatment including hydration and cooling will be initiated [5]. Subjects will remain at the CRC overnight for further observation if body temperature has not returned to pretreatment levels ± 0.5 C at the end of the test session at 6 PM.

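### The only driving restriction shown ends on the evening of the study day, before the 1-3 day period in which the protocol expects MDMA after-effects such as difficulty concentrating

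*Protocol*

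**What the plan says.** Protocol 10.4.2 (Inclusion criteria), item 7: "Participants must be willing not to drive a traffic vehicle in the evening of the study day". This is the only statement about driving in the text shown.

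On timing, 11.3 places MDMA or placebo 4 h after the 8 AM duloxetine or placebo dose, and states "The sessions end at 6 PM".

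On later effects, 14.1 says: "MDMA is expected to produce sequelae (1-3 days post MDMA) including difficulty concentrating, irritability, or slightly depressed mood in more than 10% of subjects". Section 14.2.6 adds that up to a third of subjects may "experience slightly depressed mood including emotional irritability, lack of energy, brooding and bad dreams for up to 3 days following MDMA administration", and continues: "These effects will be specifically monitored using an adverse effects check list".

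On release from the unit, section 14 says "After the test session subjects are allowed to leave only if the subjective and cardiovascular effects of MDMA have completely ceased". Section 14.2.6 says "After the test session subjects are allowed to leave only if the subjective effects of MDMA have completely ceased", which it defines as the VAS for drug effect being back within 10% of its predose value. The same section keeps subjects overnight if blood pressure, pulse or body temperature is still raised at 6 PM.

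On follow-up, 11.4.2.2 says "An additional LC is completed 24 h after MDMA/placebo in the absence of the experimenter". Subjects are next asked about adverse effects when they come for the following session.

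**The concern.** By writing criterion 7 the protocol accepts that driving should be restricted after a session. It then fixes the end of that restriction without reference to its own account of when after-effects occur. Among the sequelae in 14.1, difficulty concentrating bears on driving most directly. Lack of energy, in 14.2.6, bears on it less. A subject who follows criterion 7 exactly is free to drive throughout the days on which these effects are expected.

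What is at stake is the safety of healthy volunteers and other road users. Nothing in the estimation or testing of the trial's endpoints depends on it.

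**Working it through.** The plan gives no figure to reproduce. The check sets two time windows side by side and then asks whether another safeguard fills the space between them.

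**Inputs**
- MDMA time (11.3): 8 AM + 4 h = 12 noon.
- Session end (11.3): 6 PM, so 18 - 12 = 6 h after MDMA.
- End of the evening: taken as midnight at the latest (assumption), so 24 - 12 = 12 h after MDMA.
- After-effect period (14.1): one to three days after MDMA.

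**Comparison of windows**
- Read in hours, one to three days is 24 to 72 h after MDMA. The stated ban runs from 6 to 12 h. The two do not overlap.
- Read in calendar days, the period starts with the day after the session, at midnight. The ban then ends just as the period begins. Again they do not overlap.

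The length of any gap depends on the reading: 24 - 12 = 12 h on the first, none on the second. The absence of overlap does not. The statement in 14.2.6 gives a latest time (up to three days) but no start, so it supports the length of the period and says nothing about a gap.

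**Other safeguards**
- Release conditions (14 and 14.2.6): these are judged at the end of the session, on drug effect, blood pressure, pulse and temperature. An effect expected a day or more later cannot be detected then.
- Complaints list at 24 h (11.4.2.2): it is filled in at home, with no experimenter present. It records symptoms, and the protocol does not link it to any restriction or clearance.
- On-call physician number (14), and treatment and follow-up of adverse events (14.2.3, 14.2.5): these provide help when a subject reports a problem, but they do not restrict driving.

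**Reach of the proposed rule**
- The unconditional part ends at 24 h, which is noon on the next day. It covers the night and the following morning. On the hours reading it covers none of the 24 to 72 h period. On the calendar-day reading it covers the first morning only.
- The symptom-dependent part, from 24 to 72 h, is therefore what reaches the after-effect period.

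**The case against.** The strongest reply is that nothing here is contradictory. Criterion 7 can be read as a margin for the hours after discharge, added to release checks that already deal with the acute effects, which 14.2.6 says are gone within 5-6 h. Sections 14.1 and 14.2.6 describe slight effects on later days, and nowhere does the protocol say that these impair driving or that the driving rule was meant to cover them. Advice for the following days could sit in the consent form. Section 11.2.1 says subjects are told of the risks both verbally and in writing, and that form is not shown.

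Much of this stands. A reader might infer that the protocol knowingly lets impaired subjects drive, or might multiply the 16 subjects by the stated rates to count drivers at risk. The documents support neither. The rate in 14.1 belongs to a group of sequelae, the third of subjects in 14.2.6 refers to slightly depressed mood, and the number of subjects who drive is not given. Nor can it be said that subjects receive no wider advice.

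The reply does not change the window written into criterion 7. Consent text might add to it, but the rule as stated would still stop short of the period in which the same document expects difficulty concentrating.

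It is also fair to say that the unconditional part of the proposed rule hardly enters the after-effect period, and that the rest depends on subjects judging themselves. Both are limits of the remedy and are accepted as such.

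**Conclusion.** The point holds as a small mismatch. The stated restriction covers none of the one to three days after MDMA in which 14.1 expects sequelae, on either reading of those days, and no other text shown restricts driving then. This rests on taking the evening to end by midnight and 11.3 to mean noon for MDMA.

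Its weight is low. The effects are described as mild, a link to impaired driving is not stated, and difficulty concentrating has no frequency of its own. The change is worth making because it is cheap and aligns a rule the protocol already has with the risk it already describes. It is not evidence of a serious safety defect.

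**What to change.** Reword criterion 7 as follows: *Participants must be willing not to drive from the end of each session until 24 h after MDMA/placebo, and from then until 72 h not while they notice difficulty concentrating, fatigue or dizziness.*

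Apply it to all four sessions, since neither subjects nor staff know which ones include MDMA. Repeat it at discharge, and add it to the consent form if it is not already there.

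The 24 h length is a judgement and not derived from data in the protocol. The part from 24 to 72 h relies on self-assessment and cannot be verified. A blanket three-day ban would avoid that, but it would be heavy for effects described as slight.

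The cost is one sentence in the criteria and one at discharge. Subjects who drive need other transport until noon on the day after each session, and longer if they have symptoms.

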### Exclusion criteria

1. Chronic or acute medical condition including clinically relevant abnormality in physical exam, laboratory values, or ECG. In particular: Hypertension (>140/90 mmHg). Personal or first-grade history of seizures. Cardiac or neurological disorder.
2. Current or previous psychotic or affective disorder
3. Psychotic or affective disorder in first-degree relatives
4. Prior illicit drug use (except THC-containing products) more than 5 times or any time within the previous 2 months.
5. Pregnant or nursing women.
6. Participation in another clinical trial (currently or within the last 30 days)
7. Use of medications that are contraindicated or otherwise interfere with the effects of the study medications (monoamine oxidase inhibitors, antidepressants, sedatives etc.)

# STUDY PROCEDURES

## Schedule of Events

The schedule of events for a subject is shown on **table 1**. Subjects take part in a 2 h screening session, four 10 h test sessions, and a 1 h end of study (EOS) visit.

## Screening procedure

### Informed consent

The subjects will be informed about the study both verbally and by the approved written consent form regarding MDMA and duloxetine, the study procedures, and associated risks, in particular including those with the use of MDMA [35]. The investigator and the subject will both personally sign and date the consent form as confirmation of consent.

### Physical health

Subjects will be examined by a research physician. Basic health will be ensured by general medical examination including medical history, physical examination, ECG, and blood chemistry and hematology. Body weight will also be measured.

### Mental health

Subjects will be screened by an MD using a semi-structured clinical interview for DSM IV [36] to exclude those with a personal or family (first-degree relative) axis I major psychiatric disorder or a history of illicit drug dependence.

### History of Drug use

Occasional recreational drug use in the past is not an exclusion criterion if no adverse reactions occurred and if use was moderate and controlled. Drugs screens are primarily intended to document and control for concomitant drug use and not as a means to exclude subjects from the study. However, subjects will be asked to abstain from any illicit drug use during the study and drug screens are performed during screening and before each session. Positive screens for stimulants, opioid or hallucinogens will result in exclusion from the study (next study session). Subjects will also be asked to abstain from excessive alcohol consumption between test-sessions and in particular to limit their use to one glass on the day before the test sessions. Smokers will be asked to maintain their usual smoking habit but will not be allowed to smoke before and up to for four hours after MDMA administration. Positive screens for THC (cannabis) will be recorded but do not result in study exclusion.

### Screening laboratory tests

The following laboratory blood tests are performed at the screening examination: Na, K, creatinine, ASAT, ALAT, -GT, hemoglobin, hematocrit, white blood cell count, red blood cell count, platelet cell count. Urine drug screen (Triage-8, Biosite, Morges, CH). Urine pregnancy test.

### CYP2D6 phenotyping

Subjects will be asked to ingest a tablet of dextromethorphan (Bexin®) 25 mg in the evening of the screening day or on a day prior to the test sessions (10-11PM) and to collect and measure the amount of urine during the next 8 h (night urine plus first morning urine). Of this urine two test vials need to be sent to our laboratory in a prepared envelope.

### Genotyping

Polymorphisms in gens that code for monoamine transporters (SLC6A2A and others) contribute to interindividual variations in the clinical response to amphetamines [37]. We will collect a blood sample at the screening visit for genotyping of monoamine transporter genes. In addition genotyping of CYP enzymes are planned (CYP2D6 genotype).

### Personality

Personality traits are known to affect subjective responses to amphetamines [38]. The Multidimensional Personality Questionnaire (MPQ) [39] and the Freiburger Personality Inventory [40] will be used to assess personality traits and their potential modulatory effects on the response to MDMA.

### Menstrual cycle phase in women

Women exhibit differential subjective effects to amphetamines during the follicular as compared to the luteal phase of the menstrual cycle [41]. Therefore, female subjects will preferentially be tested during the follicular phase (day 2-14) of the cycle.

## Schedule of experimental session

**Table 2** shows the schedule of events for each experimental session. Each of the four test sessions will last 10 h from 8:00 AM to 6:00 PM. Subjects will arrive at 8:00 AM at our CRC. Subjects will take duloxetine (120 mg) or placebo the night before the study session at 8:00 PM and another dose of duloxetine (120 mg) or placebo in the morning of the study day (8:00 AM). An indwelling intravenous catheter will be inserted into a subcutaneous vein of the forearm of the nondominant arm. MDMA (125 mg) or placebo is administered 4 h after duloxetine (12:00 AM). The acute effects of MDMA are expected to last for 4 h [42, 43]. Outcome measures (see below) will repeatedly be assessed during the study session. The sessions end at 6 PM. Subjects will be under continuous medical control until the effects of the drug have completely subsided (within 4-6 h after MDMA administration).

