### Concomitant medications

Concomitant use of medications will be recorded at the screening visit and at the beginning of each study session. Subjects are asked to abstain from using drugs that may interfere with the effects of the study medications including sleeping aids, cough medications, betablocker or other substances with potentially relevant psychoactive effects. The PI may exclude subjects from study participation or reschedule sessions in the case of relevant pharmacokinetic of pharmacodynamic interactions with concomitant medications.

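### The concomitant-medication and interval adverse-event questions are placed at the 8 AM session start, 12 h after each session's first duloxetine or placebo dose, and no check is tied to that dose

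*Protocol*

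**What the plan says.** Protocol section 11.3 (Schedule of experimental session) sets the timing: "Subjects will take duloxetine (120 mg) or placebo the night before the study session at 8:00 PM". A second dose follows on the study day at 8 AM. The same section says "Subjects will arrive at 8:00 AM at our CRC" and "Each of the four test sessions will last 10 h from 8:00 AM to 6:00 PM", so a session begins at 8 AM. Section 11.5.6 (Compliance) gives the subject a medication box for each session and a reminder call on the day before; only study-day dosing is observed by staff.

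Four checks recur with each session:

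- Concomitant medication (section 11.5.4): "Concomitant use of medications will be recorded at the screening visit and at the beginning of each study session". The investigator may then exclude the subject or reschedule.
- Adverse events since the last session (section 11.4.2.2): "Subjects will also be asked to report AE between study sessions at the beginning of the next session". Section 14.2.3 instead places this assessment before the next session.
- Pregnancy (section 10.4.2): "Pregnancy tests are repeated before each study session".
- Illicit drugs (section 11.2.4): "drug screens are performed during screening and before each session".

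Section 11.1 (Schedule of Events) lists the contacts: "Subjects take part in a 2 h screening session, four 10 h test sessions, and a 1 h end of study (EOS) visit". None falls on the evening before a session.

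**The concern.** A check that can exclude a subject or move a session should come before the exposure it screens for. Section 10.4.3 excludes subjects on contraindicated or interfering medicines and names monoamine oxidase inhibitors and antidepressants. As sections 11.3 and 11.5.4 are written, someone who began such a medicine between sessions would be asked about it only after the evening dose. An adverse event that arose or persisted after the last assessment would likewise be asked about only after that dose.

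There is a smaller cost in conduct. A session rescheduled at 8 AM is rescheduled after its first blinded dose has been used, and the protocol does not say what then happens to that session's medication.

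**Working it through.** No power or sample-size formula applies. The check is clock arithmetic and a comparison of sections.

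**1. The protocol's own intervals.** Section 11.5.1 puts the first dose 12 h before the second and 16 h before MDMA.

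- 8 PM to 8 AM = 12 h.
- 8 PM to midday = 16 h.
- 8 AM to midday = 4 h.

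All three agree with the text if the stated MDMA time of 12:00 AM is read as midday, the only reading that fits 4 h and 16 h.

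**2. Position of a session-start check.** Sessions begin at 8 AM, so such a check falls 12 h after the first dose and 4 h before MDMA. Section 11.5.1 gives a duloxetine Tmax of 6 h, so it also falls 12 − 6 = 6 h after the stated time of peak concentration from that dose. Section 11.3 gives 8 AM for both arrival and the second dose and does not order the checks between them. Even the second dose is therefore only possibly preceded by a check.

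**3. Each check against the 8 PM dose.**

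| Check | Stated time | Relative to the 8 PM dose | Stated consequence |
| --- | --- | --- | --- |
| Concomitant medication (11.5.4) | session start | 12 h after | exclusion or rescheduling, at the investigator's discretion |
| Interval adverse events (11.4.2.2) | session start | 12 h after | none tied to this question |
| Interval adverse events (14.2.3) | before the next session | not fixed | none tied to this question |
| Pregnancy test (10.4.2) | before each session | not fixed | pregnancy is an exclusion criterion (10.4.3) |
| Drug screen (11.2.4) | before each session | not fixed | exclusion for some positive results |

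The first two rows need no inference. For the last three, arrival at 8 AM is the only on-site opportunity that the visit list offers, but no section states it.

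**4. Doses concerned.**

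- 16 subjects × 4 sessions = 64 evening doses.
- 16 subjects × 2 duloxetine conditions = 32 active evening doses; the other 32 are placebo.
- Interval adverse events arise only from the second session on: 16 × 3 = 48 evening doses.

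For those 48, the previous scheduled record of concomitant medication dates from the start of the preceding session, at least 10 days earlier by the separation given in section 7.2.2.

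**The case against.** The strongest reply is that much of the alarm rests on inference. A reader might conclude that all four checks take place at or after 8 AM and are all meant to gate dosing. The text does not support that:

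- Pregnancy tests and drug screens have no clock time, and Tables 1 and 2, which hold the schedules, are not shown and might settle it.
- Section 11.2.4 describes drug screens as chiefly for documentation, although some positive results do exclude.
- No gating rule is attached to the interval adverse-event question.

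A reader might also infer that a subject who reacted badly to one session is dosed for the next before anyone has asked. That is not so. The list of complaints is completed at 180 min and again at 24 h, and further events are recorded at 5 h (section 11.4.2.2). Subjects are supervised during the session and have an on-call number afterwards (section 14). Adverse events are followed up (section 14.2.5), and the investigator may withdraw a subject (section 14.4.6). What remains uncovered is an event that arises or persists later and is not reported spontaneously.

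Other protections stand. Women of childbearing potential need a negative test at entry and effective contraception, and women are tested preferentially on cycle days 2 to 14 (section 11.2.9). Subjects are asked to avoid interfering medicines and illicit drugs. Section 11.5.6 does not confine the day-before call to compliance, and it does not say that the evening dose is taken at home; off site and unobserved is as far as the text goes.

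These points narrow the concern and lower the risk. None of them supplies a stated check before the 8 PM dose, and none moves the concomitant-medication question from session start.

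**Conclusion.** The point holds in a limited form. The concomitant-medication check, which can lead to exclusion or rescheduling, and the interval adverse-event question as worded in section 11.4.2.2 are placed 12 h after the first dose of the session they concern. Followed exactly, they can inform only the second duloxetine dose and MDMA. This is a fault of sequence between sections 11.3, 11.4.2.2 and 11.5.4, and not merely a missing detail. For the pregnancy test and drug screen the protocol leaves the timing relative to that dose open; that they come too late cannot be asserted.

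The scope is 64 evening doses, 32 of them active, assuming that 16 subjects complete all four sessions. The conclusion rests on the visible text and could change if the schedule tables place a check on the day before. No bias in an endpoint or in the analysis is shown. The point deserves action because the correction is nearly free and bears on safety.

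**What to change.** Reconcile sections 10.4.2, 11.2.4, 11.3, 11.4.2.2, 11.5.4, 11.5.6 and 14.2.3 so that each check has a stated time relative to the first study capsule of the session, and so that the interval adverse-event question is timed the same way in both places. In section 11.3, state the order of the on-site checks and the 8 AM dose.

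Add two questions to the day-before call already provided for in section 11.5.6: any new medicines, and any adverse events since the last session. Record the answers in the CRF. Keep the on-site pregnancy test, the drug screen and the session-start questions as they are. What follows from a positive answer on the call is a clinical decision for the investigator to define in the protocol.

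The cost is a few lines of protocol wording, a short CRF script and a slightly longer phone call. Doses, visits and the analysis do not change.
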